### *Development and validation of algorithms*

As indicated in section 3.3, the algorithms applied in both the control and experimental condition will continually be developed during the trial with specific versions being released and evaluated throughout. During the Learning Phase and Period 1, first versions of the algorithms will be implemented which have been developed using data collected from previous studies and existing users of the Ava bracelet. Data collected during the Learning Phase will then be used to develop second versions of the algorithms which will be

implemented and statistically evaluated in Period 2. When all subject follow-up is complete and all data is collected, final versions of the algorithms will be developed. As such, the Learning Phase will primarily be used to collect both physiological and symptom data to train both algorithms, Period 1 to gain further understanding of the first version of the algorithm and enable blinded sequences, and Period 2 will be used to statistically evaluate the second version of the algorithm as specified in the primary objective.

For these analyses, the duration of implementation of different versions of the algorithms will be taken into account. As such, the performance of the implemented algorithms will be calculated using data collected during its implementation. In addition, the performance of different versions of the algorithms can be assessed by applying them retrospectively to all of the collected raw data. In this way, the algorithms will be judged as actually implemented in the trial (*de facto* estimation) and under a hypothetical condition wherein the final developed algorithm is treated as having been implemented for each subject (*de jure* estimation).

#### *Comparison between study conditions and within-subjects*

For the primary comparison between study conditions, the control condition will act as a reference group towards the experimental condition for Period 2. By directly comparing both study conditions within the crossover design, the added benefit can be assessed of including the Ava bracelet data for the detection of potential SARS-CoV-2 infections. In addition to the evaluation within Period 2, control vs. experimental comparisons will be made using both periods via application of bootstrapping methods detailed further below. In addition, a within-subjects analysis will be performed using all subjects as they will all wear and synchronise the bracelet throughout the trial. This allows for an extra within-subject analysis of the ability of the algorithm based on the symptom data with or without the bracelet data to detect early and asymptomatic SARS-CoV-2 infection.

#### *Analysis sets*

Several analysis sets will be defined which will be used for the analyses described in the following sections:

- **Intention-to-treat set:** All subjects randomized to one of the two study sequences. For the analysis, subjects will be considered part of the study sequence that they were originally randomized to. Note that when a subject has their first SARS-CoV-2 infection (as confirmed through a positive PCR/antigen or serology test), they will no longer be part of the analysis going forward because they have met the primary outcome.

- **Efficacy analysis set:** All compliant subjects randomized to one of the two study sequences, where compliance is defined as having entered symptom data in the Ava COVID-RED app on at least 80% of the days of Period 2 **and**, when in the experimental condition, having worn and synchronised the Ava bracelet on at least 80% of the days of Period 2.
- **Partial compliance set:** All subjects randomized to one of the two study sequences that were partially compliant; which is defined as having entered symptom data in the Ava COVID-RED app on at least 80% of the days of Period 2 **or**, when in the experimental condition, having worn and synchronised the Ava bracelet on at least 80% of the days of Period 2.
- **Safety analysis set:** All subjects who were randomized and received an Ava bracelet.

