### 2.2 Secondary Objective(s):

1. To assess the health economic utilization of a wearable device and mobile application as measured by endpoints such as:
  - a. Number of tests for suspected SARS-CoV-2 infections
  - b. Number of hospitalizations
  - c. Number of ICU events
  - d. Number of days requiring breathing support (e.g. oxygen and/or ventilation)
2. To determine the incidence of SARS-CoV-2 infection during the study
3. Identify which features of the Ava bracelet and Daily Symptom Diary are the most predictive features
4. Assess the independent predictiveness of an algorithm derived from physiological data gathered by the Ava bracelet in addition to self-reported daily symptom data
5. To assess the time from algorithm indication to symptom onset in the subject
6. To assess the time from algorithm indication to testing of the subject
7. To determine how taking antipyretic medication affects physiological parameters among subjects using the Ava bracelet and Daily Symptom Diary
8. To determine how self-reported vaccinations cause changes in biophysical parameters from subject's given baseline measurements
9. To correlate the longitudinal symptoms reported by study subjects confirmed to have COVID-19 with changes over time in their physiological data
10. To characterise longitudinal symptoms and recovery dynamics reported by the study subjects to the presence or absence of lab-confirmed SARS-CoV-2 infection
11. To assess the adherence to daily symptom diary completion and Ava bracelet wearing and synchronising over time

12. To determine the time necessary to establish baseline physiological parameters per subject in the Learning Phase of the study
13. To determine if retrospective identification of the moment of potential SARS-CoV-2 infection is possible for subjects who are seropositive at the end of a period but were negative at baseline and did not receive an alert to get tested during the study
14. To determine the rate of breakthrough and asymptomatic COVID-19 infections among vaccinated individuals
15. To assess the influence of self-reported COVID-19 vaccinations on compliance to study procedures

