### 3.4 Algorithm indicators

In both study conditions, the respective algorithms will alert subjects about their real-time health status in the Ava COVID-RED app through 3 types of indicators:

- **Green light:** No deviations in physical health (symptoms or biophysical parameters) detected. No recommendation is given to the subjects.
- **Yellow light:** Subjects are experiencing some symptoms but not those strictly defined as related to COVID-19 or biophysical parameters deviate slightly from baseline but do not meet the threshold value for a Red light indicator. The Yellow light indicator asks participants to consider self-isolating and keeping an eye on the Ava COVID-RED app the following day.
- **Red light:** Significant changes in biophysical parameters have been detected or symptoms that meet the RIVM criteria have been reported. The Red light indicator suggests subjects consider getting tested for COVID-19 and/or to consult a medical professional.

In all cases of a red-light indicator, subjects will receive the following generic message on the home screen of the Ava COVID-RED app after synchronising their bracelet or logging their symptoms within the last 24 hours:

“Your data suggests changes in physiological parameters and/or symptoms that might be related to a potential COVID-19 infection. Please consider seeking testing and/or input from a medical professional.”

When subjects obtain a positive PCR/antigen or serology test result during the study, they will continue to be in the study but will be moved into a so-called “COVID-positive” mode in the Ava COVID-RED app. This means that they will no longer receive recommendations from the algorithms but can still contribute and track symptom and bracelet data.

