#### 8.1.2 Secondary study parameters/endpoints (if applicable)

Additional endpoints will be collected for analysis of the secondary objectives as listed in Section 2.

*Study condition compliance (collected with Ava COVID-RED app)*

- Duration of Ava bracelet use (amount of days between first day of synchronised data and last day of synchronised data)
- Duration of daily symptom diary use (amount of days between first day completed symptom data and last day completed symptom data)
- Compliance rate: percentage of days (as compared to duration of use) that Ava bracelet was worn and synchronised.
- Compliance rate: percentage of days (as compared to duration of use) that symptoms were entered into the Daily Symptom Diary of the Ava COVID-RED app

*Longitudinal characteristics of study population (collected with Ava COVID-RED app)*

- Number/percentage of non-antipyretic and antipyretic medication days
- Number and type of vaccination events
- Number/percentage of days with alcohol consumption
- Number/percentage of days with recreational drug usage
- Number/percentage of days with period (menstruating women only)
- Number of pregnancy events (menstruating women only)

*Overall incidence of SARS-CoV-2 (collected through self-reporting of PCR/antigen test results in the Ava COVID-RED app and serology results)*

- SARS-CoV-2 cumulative incidence by condition and by stratum

*Healthcare Resource Utilization (collected throughout the study through bi-weekly surveys in COVID-RED web portal, structured interviews, and Ava COVID-RED app)*

- Number of COVID-related contacts from subjects to their general practitioner (GP)
- Number and duration of COVID-related hospitalization episodes
- Number and duration of COVID-related intensive care unit (ICU) episodes
- Number and duration of COVID-related supported breathing intervention
- Number and percentage of subjects with each reported medication used during hospitalization (WHO Drug Dictionary [WHO-DD])

*COVID-19 Testing (collected throughout the study through bi-weekly surveys in COVID-RED web portal and Ava COVID-RED app):*

- Number of tests conducted by GGD
- Number of provided PCR kits used
- Number of tests conducted due to red-light indicator of Ava COVID-RED app
- Time between first recommendation for testing and contact with GGD
- Time between first recommendation for testing and contact with study team for PCR sample kit

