### 10.5 Analysis of Secondary Endpoint(s)

Secondary study endpoints mentioned in section 8.1.2 will be analysed and compared within the Intention-to-treat, Efficacy analysis and Partial compliance sets within each period. Where deemed relevant, analyses will also be executed within selected subsets of these analysis sets. Specific subsets will be listed within the Statistical Analysis Plan. Results will be presented in tables where possible. Where percentages are to be calculated, the number of subjects in the condition within the specified analysis (sub)set will be used as the denominator.

Where assumptions are met, Cochran-Mantel-Haenszel tests stratified by the risk strata will be performed in each period for multiple secondary endpoints, including:

- The number and percentage of subjects that obtained a red-light indicator by the applied algorithm at least once.
- The number and percentage of subjects with at least one positive SARS-CoV-2 virus test result during follow-up.

- The number and percentage of subjects that donated a blood sample for a SARS-CoV-2 antibody test at baseline, after the Learning Phase and after both periods.
- The number and percentage of subjects with a positive SARS-CoV-2 antibody test at baseline, after the Learning Phase and after both periods.
- The number and percentage of subjects with at least one positive SARS-CoV-2 virus test result during each period OR a positive SARS-CoV-2 antibody test result within those periods.
- The number and percentage of subjects without a positive SARS-CoV-2 virus test result during each period AND a negative SARS-CoV-2 antibody test result within those periods.
- The number and percentage of subjects that have reported experiencing each of the symptoms listed in the Ava COVID-RED app at least for one day during the study.
- The number and percentage of subjects that have reported experiencing each of the symptoms corresponding by the RIVM guidelines at least for one day during the study.
- The number of subjects who reported a positive SARS-CoV-2 virus test during the study and the percentage of subjects who reported a positive SARS-CoV-2 virus test during the study, with the number of subjects ever receiving a PCR test during the study as the denominator.

Where assumptions are met, t-tests will be performed in each period for multiple secondary endpoints, including:

- The average and median number of times a single subject obtained a red-light indicator by the applied algorithm.

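### The Intention-to-treat set removes subjects at first confirmed infection without limiting this to detection, yet section 10.5 uses that set for secondary endpoints that mostly arise after infection

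*Protocol*

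**What the plan says.** Section 10 (Analysis sets) defines the ITT set as all randomised subjects, analysed in their assigned sequence, and adds a note inside that definition. The trigger is "when a subject has their first SARS-CoV-2 infection (as confirmed through a positive PCR/antigen or serology test", and the consequence is that "they will no longer be part of the analysis going forward because they have met the primary outcome". The Efficacy and Partial compliance definitions carry no such note.

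Section 10.5 states that the secondary endpoints of 8.1.2 "will be analysed and compared within the Intention-to-treat, Efficacy analysis and Partial compliance sets within each period". The 8.1.2 list includes COVID-related GP contacts, "Number and duration of COVID-related hospitalization episodes", "Number and duration of COVID-related intensive care unit (ICU) episodes", "Number and duration of COVID-related supported breathing intervention", and the number and duration of each reported symptom.

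Section 3.4 says of subjects with a positive test that "they will continue to be in the study but will be moved into a so-called" COVID-positive mode. They get no further algorithm recommendations but can go on supplying symptom and bracelet data (also 8.4.13). Sections 8.4.15 and 8.4.16 collect hospital episodes every two weeks, followed by a structured interview.

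**The concern.** Leaving the risk set at first infection is correct when the outcome is first detection. It is not correct when the outcome is what happens to the infected person afterwards. Secondary objectives 1b-1d (hospitalisation, ICU, breathing support) depend on follow-up after infection, and so does the symptom-duration comparison that 10.5 itself lists among its t-tests.

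As written, one set definition serves both purposes. A programmer who follows it would discard data that the trial has deliberately continued to collect. ITT is also the only one of the three sets in 10.5 that does not depend on compliance, so it is the set a reader would trust most for comparing healthcare use between conditions.

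**Working it through.** The protocol gives no figure to reproduce here. The check sets the sections side by side and then sizes the narrower reading under stated assumptions.

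**1. Scope of the rule.** The Analysis sets text introduces the sets for use in the sections that follow. The removal note sits in the ITT definition and names no endpoint. Section 10.5 then uses the ITT set for every 8.1.2 endpoint, so nothing in the text exempts healthcare use or symptom duration.

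**2. Two readings of when a subject leaves.**

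| Reading | Source | Effect on the ITT analysis of post-infection endpoints |
|---|---|---|
| From the date of confirmation | Analysis sets, taken literally | Data after the first positive test are omitted. What precedes confirmation stays, for example an episode whose infection is found only by end-of-period serology. |
| From the next period | 4.4 and 10.4 | The period of infection is kept in full. Later periods are excluded, so a Period 1 infection loses its Period 2 follow-up. |

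**3. Size under the next-period reading.** Assumptions, none of them from the protocol: a 3-month period is 91 days; Period 1 infections are confirmed evenly over it; an episode starts, or is still running, L days after confirmation. The episode reaches Period 2 if confirmation falls in the last L days of Period 1, so the share affected is L/91.

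- Admission starts 8 days after the test: 8/91 = 8.8%. These episodes begin in Period 2 and are lost entirely.
- Episode extends to day 10: 10/91 = 11.0%.
- Episode extends to day 20: 20/91 = 22.0%.

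The last two shares include episodes that began in Period 1, which are still counted but have their duration cut. Infections in Period 2 have no later period and lose nothing this way, so the share over both periods is smaller. The protocol gives neither an admission rate nor the timing of admission relative to the test, so no count of lost episodes can be derived.

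**4. Whether the other two sets can stand in.** Both require 80% compliance over Period 2: 0.80 × 91 = 72.8, so 73 days are needed, 18 may be missed, and 19 missed days fail.

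| Set | Control condition in Period 2 | Experimental condition in Period 2 |
|---|---|---|
| Efficacy | diary | diary and bracelet |
| Partial compliance | diary | diary or bracelet |

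The Efficacy set is harder to enter for experimental subjects than for controls; the Partial compliance set is easier. Both also select Period 1 episodes on behaviour in Period 2. Diary entries may be made up to 7 days late (8.4.9), so a continuous diary absence of 18 + 7 = 25 days can still pass. A longer absence fails, and the protocol gives no similar allowance for missed bracelet nights.

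**The case against.** The strongest reply is that the rule was never meant to reach these endpoints. Its stated reason, that the subject has met the primary outcome, points to detection. Where the protocol spells out the exclusion (4.4 and 10.4), it works by period. Section 10.5 plans end-of-period antibody summaries that would lose subjects with a positive virus test if they left on the test date. The other two sets carry no removal rule, and an illness of 10-20 days would often not break the 80% threshold. Hospital, ICU and breathing-support measures appear in neither the Cochran-Mantel-Haenszel nor the t-test list, so their detailed analysis is left to the SAP.

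Much of this stands. A reader might infer that these endpoints cannot be reported from any planned set, or that the tables would show near-zero utilisation in both conditions. The protocol does not support that: two of the three sets keep post-infection data, and the period-level reading keeps same-period episodes. Nor does it support the view that seriously ill subjects would generally fail the compliance sets, or that the objectives on symptoms and recovery in confirmed cases are out of reach. Section 10.5 allows SAP-defined subsets, and recovery is an objective, not a named 8.1.2 endpoint.

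The reply does not remove the conflict. Section 4.4 concerns sample size and 10.4 the combining of a test statistic over periods; neither limits the ITT note to detection. The protocol itself fixes both the definition and its use in 10.5, so this is not merely detail deferred to the SAP. The period-level reading still drops Period 2 follow-up of Period 1 infections, and no text says to which condition such an episode belongs.

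**Conclusion.** The point holds as a conflict affecting secondary endpoints. Followed literally, the ITT analysis omits COVID-related healthcare use and symptom duration after the first positive test. Under the period-level reading it loses or truncates roughly 9-22% of episodes from Period 1 infections, given evenly spread confirmation dates, lags of 8-20 days and a 91-day period. The two readings give very different event counts, and the text does not choose between them for these endpoints. The compliance-based sets are not an unselected substitute. The primary detection analysis is unaffected, and severity is moderate.

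**What to change.** Amend sections 10 and 10.5 as follows:

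- Define the ITT set as all randomised subjects, in their assigned sequence, with no removal clause.
- Move removal at first confirmed infection into 10.2-10.4, worded as leaving the at-risk set for detection.
- State in 10.5 that healthcare-utilisation and symptom-duration analyses use all follow-up after infection.
- State in advance to which period and condition an episode after infection is attributed. The condition in force at infection is one option; the choice is the sponsor's, but it should be fixed before analysis.

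This is a wording change. Infected subjects already stay in follow-up, so no new data are needed.

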### 10.2 Primary Analysis of Primary Endpoint(s)

The primary analysis of the primary endpoint will compare the performance of the algorithm applied in each study condition to detect if subjects were ever infected during Period 2. This analysis will be performed on both the Intention-to-treat and Efficacy analysis sets, within each period and stratified per risk group. For the subjects within each study condition, the daily prediction of possible SARS-CoV-2 infection and the results of PCR/antigen and serology tests will be summarized over the whole period per subject to determine (1) if a subject was ever judged to have a high risk for a potential SARS-Cov-2 infection (i.e. received a red-light indicator from the Ava COVID-RED app), and (2) if a subject was ever confirmed to have a SARS-CoV-2 infection by PCR/antigen or serology testing. For this comparison, parameters such as sensitivity, specificity, positive predictive value, and negative predictive value will be calculated.

To confirm whether a subject was ever infected in Period 2 with SARS-CoV-2, the serology status at the end of Period 2 for each subject still alive at that time will be used as the gold standard. Those with a previous positive test result will be excluded from the analysis. For subjects not alive at the end of Period 2, the status of available SARS-CoV-2 virus tests during Period 2 will be used (positive at any time) and for those without any test results, a physician diagnosis during Period 2 will be accepted provided there was a supportive lung CT scan used. All other subjects will be summarized for transparency but excluded from the estimation for sensitivity, specificity, positive predictive value and negative predictive value.

The following quantities are needed for these statistics:

- **Predicted condition positive:** The total number of subjects that obtained a red-light indicator from the Ava COVID-RED app at least once during Period 2.
- **Predicted condition negative:** The total number of subjects that never obtained a red-light indicator from the Ava COVID-RED app during Period 2.
- **Condition positive:** The total number of subjects who tested positive at least once using SARS-CoV-2 virus testing during Period 2 OR who had a positive serology test at the end of Period 2.
- **Condition negative:** The total number of subjects who never tested positive for the SARS-CoV-2 virus during Period 2 AND who had a negative serology test at the end of Period 2.

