### 10.3 Secondary Analysis of Primary Endpoint(s)

The secondary analysis of the primary endpoint will compare which of the two algorithms between study conditions has superior performance characteristics for detecting early or asymptomatic SARS-CoV-2 indication or infection. Time-to-event analyses will be performed using the Intention-to-treat, Efficacy analysis and Partial compliance set. Analyses will be performed within each study period and stratified per risk group. Kaplan-Meier plots will be

constructed for visual support. An event will be defined as either the first indication (red-light indicator from the Ava COVID-RED app) or first infection (as confirmed by PCR/antigen testing) of SARS-CoV-2 of a subject during the study period. Subjects lost to follow-up or reaching the end of the period without infection will be censored. Stratified log-rank tests will be performed within each period to assess whether the experimental condition shows a statistically significant improvement (or lack thereof) in time to indication or infection as compared to the control condition with a median difference used to state the effect size. If the median is not yet reached in either study condition then a different quantile will be used. If other variables are to be taken into account, Cox proportional hazards models will be used where assumptions are met.

This same analysis will also be performed retrospectively in all subjects where the time to first indication or infection will be assessed using the algorithm based on only the symptoms data or both the symptoms and bracelet data within each subject. Because the measurement methods are correlated (both physically and in data collection), a within-person comparison can be made using paired statistical methods. If assumptions are satisfied, a Wilcoxon signed rank test will be used for this analysis; otherwise, other paired tests will be considered.

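### The Efficacy and Partial compliance sets apply the bracelet criterion only in the experimental condition and only to Period 2 days, so the compared arms are selected by different rules and Period 1 is selected by later behaviour

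*Protocol*

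**What the plan says.** Protocol section 10, under Analysis sets, defines both compliance-based sets. The diary part applies to every subject: "having entered symptom data in the Ava COVID-RED app on at least 80% of the days of Period 2". The bracelet part applies only "when in the experimental condition, having worn and synchronised the Ava bracelet on at least 80% of the days of Period 2". The two parts are joined by AND in the Efficacy set and by OR in the Partial compliance set. Both count Period 2 days, and no compliance rule is given for Period 1.

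The sets are used widely. For the primary analysis, section 10.2 says: "This analysis will be performed on both the Intention-to-treat and Efficacy analysis sets, within each period and stratified per risk group". Section 10.3 says: "Time-to-event analyses will be performed using the Intention-to-treat, Efficacy analysis and Partial compliance set", and adds: "Analyses will be performed within each study period and stratified per risk group". Under section 10.5 the secondary endpoints are "analysed and compared within the Intention-to-treat, Efficacy analysis and Partial compliance sets within each period".

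Bracelet data exist in both conditions. The text on comparisons between conditions and within subjects says of all subjects that "they will all wear and synchronise the bracelet throughout the trial". Section 8.1.2 defines a bracelet compliance rate without reference to condition, and the low-compliance withdrawal rule in section 8.5.1 does not depend on condition either.

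**The concern.** Randomisation makes the two conditions comparable in the people they contain. A compliance set gives up some of that, but it can stay roughly balanced if the same filter is applied to both arms. Here the filters differ: the experimental arm is narrowed in one set and widened in the other, while the control arm is identical in both. People who wear and synchronise a bracelet reliably may also log symptoms more fully, or receive alerts at a different rate. If so, a difference in sensitivity or specificity in the Efficacy set mixes the algorithm's effect with the effect of who was kept. The Efficacy set is one of the two sets named for the primary analysis, and section 10.2 does not rank them.

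Period 1 has a further problem. Membership of a Period 1 analysis is decided by what subjects do three months later, after some of them have had the outcome.

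**Working it through.** The protocol gives no expected compliance and no set size, so there is no figure to reproduce. The check applies the definitions as written, then illustrates what they could do.

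**Step 1. The rules by sequence.** Let D = diary on 80% or more of Period 2 days, and B = bracelet on 80% or more of Period 2 days. Section 3.1 gives Sequence 1 experimental then control, and Sequence 2 control then experimental. The bracelet rule attaches to subjects who are experimental in Period 2, that is, Sequence 2.

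| Analysis | Sequence 1 | Sequence 2 |
|---|---|---|
| Period 2, Efficacy | control: D | experimental: D and B |
| Period 2, Partial | control: D | experimental: D or B |
| Period 1, Efficacy | experimental: D | control: D and B |
| Period 1, Partial | experimental: D | control: D or B |

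The Period 1 rows are the natural reading of a rule worded for Period 2. The bracelet filter then falls on the Period 1 control arm.

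**Step 2. Share of each arm kept.** Assume P(D) = P(B) = 0.75.

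- Control, both sets: P(D) = 75%.
- Experimental, Efficacy: P(D and B) lies between 0.75 + 0.75 − 1 = 50% and min(0.75, 0.75) = 75%; if independent, 0.75 × 0.75 = 56%.
- Experimental, Partial: P(D or B) = 0.75 + 0.75 − P(D and B), which lies between 75% and 100%; if independent, 94%.

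With 80% for each and independence, per 10,000 randomised, control keeps 8,000 in both sets and experimental keeps 6,400 (Efficacy) or 9,600 (Partial).

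**Step 3. When this produces bias.** Unequal set sizes alone do not. The Efficacy set compares D-and-B people with D people, so bias arises only if, among infected or among uninfected subjects, alert rates differ between those groups. If everyone who meets D also meets B, the groups coincide. The Partial set is the mirror case: it is harmless if everyone who meets B also meets D.

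**Step 4. Illustration of size.** A simulation gave both arms the same alert rule, so the true difference is 0. Assumptions: 10% infected; alert probability 75% in infected and 20% in uninfected subjects at the average adherence level; 80% meeting D; 60% or 80% meeting B; a shared adherence trait (loading 0.5 or 0.7 on compliance) that also raises the chance of an alert (0.3 or 0.5 on the probit scale). Six scenarios were run with 8 million subjects each.

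| Set | Sensitivity, experimental − control (points) | Specificity, experimental − control (points) |
|---|---|---|
| Intention-to-treat | about 0 | about 0 |
| Efficacy, as written | +1.2 to +4.6 | −1.2 to −4.4 |
| Partial, as written | −0.4 to −1.7 | +0.5 to +1.5 |
| Either set, same rule in both arms | within 0.13 | within 0.13 |

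For scale, Tables 3 and 4 of section 4.4.1 consider differences of 1% to 7% in sensitivity and 1.5% to 3% in specificity. The signs follow from assuming that adherent people receive more alerts; the opposite assumption would reverse them.

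**Step 5. Period 1 infections.** These subjects form the sensitivity denominator in Period 1. They leave the Period 2 analysis (sections 4.4 and 10.4), yet enter the Period 1 Efficacy set only by complying in Period 2. Those with a known positive result spend Period 2 in COVID-positive mode without further indicators (sections 3.4 and 8.4.13), though they are still asked to log symptoms and wear the bracelet.

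**The case against.** The arm-specific rule has a rationale. Under section 3.2, bracelet data feed the algorithm only in the experimental condition and the Learning Phase. A control subject with a full diary and a neglected bracelet has received the control condition in full, so in a per-protocol sense nothing is missing. This explains the rule, but it does not make the filtered arms comparable.

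The primary analysis is also run on the Intention-to-treat set, which this rule does not touch. The Partial compliance set is not used in section 10.2; it appears in sections 10.1, 10.3 and 10.5. The primary comparison sits in Period 2, so the Period 1 gap affects supporting analyses. All of this stands and limits the weight of the point.

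Three stronger readings are tempting, and the documents do not support them.

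- A reader might infer that the experimental arm of the Efficacy set is less ill. Nothing in the protocol links bracelet compliance to illness in that direction.
- A reader might infer that everyone infected in Period 1 is in COVID-positive mode during Period 2. The end-of-Period-1 sample is analysed only if the end-of-Period-2 sample is positive (sections 3.6 and 8.4.8). Infections found only by serology therefore come to light after Period 2, and those subjects stay in normal mode during it.
- A reader might connect the sets with the endpoint in section 8.1.2, "Compliance rate: percentage of days (as compared to duration of use) that Ava bracelet was worn and synchronised". Set membership counts Period 2 days, not duration of use, so that denominator has no bearing here.

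**Conclusion.** The point holds on the wording alone: the arms are selected by different rules in both compliance-based sets, and Period 1 membership is decided by Period 2 behaviour, with the bracelet filter on the Period 1 control arm. The data collection does not require this.

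The consequence is conditional. If bracelet adherence among the subjects concerned is related to symptom reporting or alerts, the Efficacy-set difference is partly selection. Its size and direction cannot be derived from the protocol. The figures of about 1 to 5 points rest wholly on the assumptions listed, and the favourable limit is zero. It would go too far to say that the primary result is biased: the Intention-to-treat analysis is unaffected. What remains open is which of the two sets carries the primary conclusion, since section 10.2 names both without an order.

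**What to change.** Apply one rule in both conditions. Efficacy set: diary and bracelet each on at least 80% of days. Partial compliance set: either one on at least 80% of days. Assess the rule on the days of the period being analysed, so that Period 1 has its own definition.

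Shorten the denominator for death only. Section 10.2 classifies subjects who die in Period 2, but with a period of about 90 days (assumed for 3 months) the threshold is 0.80 × 90 = 72 days, which an early death makes unreachable. Do not end the denominator at a positive test. Subjects who test positive are still asked to log and wear the bracelet (section 8.4.13), and if one condition prompts earlier testing, a window ending at the test would differ by arm and bring back selection by outcome.

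State in section 10.2 that the primary conclusion rests on the Intention-to-treat set, with the Efficacy set supportive.

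The cost is two set definitions and one sentence; the data are already collected. The control Efficacy set becomes smaller and no longer represents control subjects who complied with the diary alone.
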